**Fig. 1. A bubble CPAP circuit connected to an infant by close-fitting nasal prongs**

[figure not shown]

An inexpensive form of bubble CPAP can be made with standard nasal prongs. The method is shown in **Figs 2 & 3**. This system is used in several hospitals in Asia (e.g. Dhaka Hospital of icddr, b in Bangladesh) [10].

This locally made (Bangladesh) bubble CPAP will be reproduced in Ethiopia during the study period. The height of the bubble CPAP bottle ( filled with water during its use for the

patient) is 17 cm, radius is 17 cm and diameter is 7.5 cm. Length of the tubing from the oxygen source up to the water filled plastic bottle ranges from 230 to 300 cm. A gas (oxygen) flow rate of 5–10 L/min is required for older children with pneumonia [10], while 3–4 L/min may be sufficient to generate CPAP in small neonates. In neonates born < 32 weeks' gestation, pure oxygen is not safe, as a high concentration can cause retinopathy of prematurity. Thus, another source of air flow, such as an air compressor or an oxygen blender, is required for premature infants. In older infants, who require a higher flow to generate CPAP, use of a 10 L/min oxygen concentrator is efficient.

**Fig.2. An inexpensive bubble CPAP set up with modified nasal prongs [11].**

[figure not shown]

**Fig. 3. Bubble CPAP with inexpensive modified nasal prongs can be run with an oxygen concentrator [11].**

[figure not shown]

## 1.5 Literature Review

Most of the studies in evaluating the efficacy of bubble CPAP were done in newborns with acute respiratory distress syndrome both in developed and developing countries [11,12]. However, a recent systematic review identified 10 studies which included children with features of severe pneumonia [13]: four publications included data from developed countries such as two from USA [14,15], one each from United Kingdom [16] and Australia [17] while six other publications from developing countries such as three from India [18-20], one each from Fiji [21], Brazil [22], and 4 rural hospitals from Ghana (RCT) [23] focused on children beyond neonatal period.

All the ten studies were prospective and five among 0-28 days group [14,15,17,19,22] and one among >28 days group [23] were RCTs. These 10 studies evaluated the efficacy of BCPAP involving 3164 children: 3059 in children aged 0-28 days and 105 children >28 days old. The study methodologies, the outcomes recorded and results were heterogeneous, although severe respiratory distress (severe dyspnea, or grunting or severe chest retraction and/or hypoxemia) was the common component of all these prospective studies. Children treated with BCPAP therapy compared to other forms of oxygen therapy (head box oxygen, historical control, delayed BCPAP, or conventional oxygen therapy) in four of these studies (2 in children 0-28 days [17,21] and other in children >28 days [18,23]) had better outcomes ( $p < 0.05$ ). Primary outcomes were

comparable between BCPAP and ventilator driven CPAP in three RCTs in children 0-28 days old [15,19,22]. The primary outcomes of rest of the two studies treated with BCPAP oxygen therapy compared to low flow oxygen or variable flow nasal CPAP therapy in children aged 0-28 days were also comparable ( $p>0.05$ ) [14,16].

On the basis of knowledge gap found from the systematic review in treating children with severe pneumonia and hypoxaemia with bubble CPAP especially in children beyond neonatal period, the Bangladesh trial was conducted which found a beneficial effect of bubble CPAP in these children. The trial done in Bangladesh showed that, among the children who received bubble CPAP for the treatment of severe pneumonia some children developed abdominal distension, and nosocomial infection, however, these adverse events were similarly observed with WHO standard low flow oxygen therapy in the same trial [11]. It is also important to note that bubble CPAP has been used routinely to support nearly 1,000 children with severe pneumonia and hypoxemia at the icddr,b hospital in Bangladesh with beneficiary outcome almost consistent with the trial outcome [24].

After the end of Bangladesh trial, an observational prospective study done in 77 Malawian children (1 week to 14 years) with progressive acute respiratory failure revealed that forty-one (53%) patients survived following bCPAP treatment, and an HIV-uninfected single-organ disease subgroup demonstrated bCPAP success in 14 of 17 (82%) [25].

Another prospective study, conducted in the Pediatric Emergency Unit of a teaching and referral hospital in North India which included 330 children (110 put on bubble CPAP) with clinical pneumonia and hypoxemia aged 1 month–12 years, they compared bubble CPAP with low flow oxygen and revealed that fifty-three children (25.9%) on low flow oxygen therapy were shifted to bCPAP for worsening distress and hypoxemia. There were a total of nine deaths (2.7%) in the study cohort; all deaths occurred in intubated children, of which only one child was initially in bCPAP group [26].

Another study done in 120 children under 2 years with moderate to severe lower respiratory tract infection revealed that bubble CPAP was successful in 72% of children [27].

A recent literature review which included 45 studies (17 clinical trials, 11 literature reviews, 10 technical assessment, three reports of real world implementation in low resource settings, three cost analysis, one case report) also concluded that CPAP is a safe and effective method of treating infants and young children with life threatening respiratory distress and can be successfully adapted for use in resource limited settings [28].

A most recent meta-analysis involving eight RCTs that compared bubble CPAP with high flow nasal cannula and WHO standard low flow oxygen therapy revealed that bubble CPAP was more beneficial than high flow nasal cannula and low flow oxygen therapy in treating under-five children with severe pneumonia and hypoxemia [30].

## 2. Rationale of the study

The provision of mechanical ventilation for hypoxaemic children in developing countries through endotracheal intubation, is not available, feasible or affordable [11]. Nevertheless, a recent finding from a clinical trial in Bangladesh showed that oxygen therapy delivered by ultra low cost bubble CPAP is a possible alternative. According to [name] et al., use of bubble CPAP significantly improved treatment failure and mortality outcomes in children with very severe pneumonia and hypoxaemia compared to those with standard low-flow oxygen therapy [10].

In countries like Ethiopia, where low-flow oxygen therapy is the only respiratory support for most of the children with severe pneumonia and hypoxaemia, having simple and effective methods of providing additional respiratory support could substantially reduce deaths from pneumonia. Bubble CPAP works by generating positive-end-expiratory pressure connecting the expiratory limb of a breathing circuit to a tube, which is submerged in water [11]. In the Bangladesh study, bubble CPAP, very simple to use and inexpensive, has been shown to be as effective as high-flow oxygen therapy but had better outcomes compared to WHO standard low flow oxygen therapy [10].

However, the feasibility and acceptability of bubble CPAP were not evaluated in childhood severe pneumonia in developing country set-ups, moreover, effectiveness of bubble CPAP has never been assessed for children with severe pneumonia in developing countries at a district hospital level where availability of ventilators and other respiratory support devices and high calibre professionals are scarce despite providing care for quite a number of children with severe pneumonia and hypoxemia. This implementation research comprising of a multicentre trial has been designed to have potential policy change for the management of childhood severe pneumonia and hypoxemia nationally and globally.

The use of traditional RCTs has a problem of speed, intense monitoring with high manpower and cost due to its efficacy nature and rarely produces findings that are directly put into practice. Recently concluded RCT in Bangladesh on bubble CPAP that was associated with significant reduction in mortality and treatment failure among Bangladeshi children having severe pneumonia and hypoxemia, was a single centre trial in an urban hospital, and the trial was conducted with intensive monitoring and additional study personnel.

Policy makers like WHO cannot change their policy until the Bangladeshi study results are reproducible in real life scenario of other country especially in government hospitals where manpower and monitoring are less, although a recent study with larger sample in Ghana supported the Bangladesh study [29]. It is therefore critical to study whether the study results are reproducible in other developing country settings. As the Ethiopian government health staff visited icddr, Dhaka hospital and were impressed with the innovative low-cost approach of bubble CPAP in treating children with severe pneumonia and hypoxemia, they became interested to implement this low cost innovation in Ethiopian hospitals as resources are less there and treatment of hypoxemia in children with severe pneumonia is still done by standard low flow oxygen.

Cluster randomized controlled trials with implementation design, reasonably inform decisions about practice, address questions of major clinical and public health importance and produce results that can be generalized and applied in usual care settings. Because they produce real-world evidence, they help to close the translation gap between discovery and practice. However, as we are intending to perform this trial in hospitals where we will have the availability of pediatricians and will have dedicated corners for the study subjects, it will be a hybrid effectiveness trial with elements of both efficacy and effectiveness.

Therefore, we aim to investigate the feasibility and acceptability of bubble CPAP in two tertiary hospitals in Stage I and two district hospitals in Stage II, and effectiveness of bubble CPAP in Stage III with a cluster randomized trial for treatment of children with severe pneumonia. In Stage III the controls will be the children treated with the WHO standard low-flow oxygen therapy. Primary outcome will be death and secondary outcome will be treatment failure among children hospitalized with severe pneumonia in Ethiopia using a cluster randomized controlled clinical trial design of an implementation study. In all the hospitals where the studies in the different stages will be conducted, pediatricians and dedicated corners for the study subjects will be available.

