|                                                   |                                                                                                                                                                                                                                                                                                                                                                                                                                                                                                                                                                                                                                              |
|---------------------------------------------------|----------------------------------------------------------------------------------------------------------------------------------------------------------------------------------------------------------------------------------------------------------------------------------------------------------------------------------------------------------------------------------------------------------------------------------------------------------------------------------------------------------------------------------------------------------------------------------------------------------------------------------------------|
|                                                   | 
-Continuous variables will be analyzed using the Student t-test or the Mann-Whitney test as appropriate.
 
-The primary outcome of the study is treatment failure and the secondary outcomes are death, pneumothorax, abdominal distention, nasal trauma, aspiration pneumonia.
 
-Primary and secondary outcomes will be compared by calculating relative risks (RRs) and their 95% confidence intervals.
 
- Log-linear binomial regression will be applied to adjust for covariates to evaluate the true impact of bubble CPAP in evaluating primary and secondary outcomes and to adjust for baseline differences.
 |

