### 3. Research questions

1. How feasible, acceptable, and safe is bubble CPAP in treating children having severe pneumonia as perceived not only by patients' care-givers but also by physicians and nurses in the initial two stages?
2. How effective, feasible, acceptable, and safe is bubble CPAP for the treatment of young children under five with severe pneumonia compared to the WHO standard low-flow oxygen therapy in reducing death (primary outcome) and treatment failure (secondary outcome) among hospitalized children in district hospitals in Ethiopia?

3. How much resource and time is needed to institutionalize and maintain bubble CPAP as a routine practice in the health system?
4. What are the main potential challenges in using bubble CPAP at different levels of health care delivery system?

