#### Secondary Objectives

- To assess the feasibility, acceptability, and safety of bubble CPAP in treating childhood severe pneumonia in two tertiary hospitals in Stage I, in two district hospitals in Stage II

- To examine the programmatic and behavioral acceptability of bubble CPAP at various health care levels (primary to tertiary) in Ethiopia in first two stages
- To identify and predict implementation level challenges and bottle necks of scaling up bubble CPAP to district level facilities
- To determine the effectiveness of bubble CPAP in reducing deaths in children admitted to frontline district hospitals with severe pneumonia and hypoxaemia compared to WHO standard flow oxygen therapy up to the maximum flow that can run through nasal oxygen cannula.

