## Primary outcome

The primary outcome of the study is treatment failure. According to this protocol treatment failure will be declared if any of the following criteria is met:

- B. Presence of severe hypoxemia ( $\text{SpO}_2 < 85\%$ ) at any time after at least one hour of intervention plus respiratory distress when the child is receiving BCPAP/LF  
OR,
- C. If the patient developed the indication of mechanical ventilation when the child is receiving BCPAP/LF  
OR,
- D. If the patient died during hospitalization or within 72 hours of left against medical advice (LAMA)  
OR,
- E. If the patient left against medical advice (LAMA) when the patient is still on study intervention

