## Secondary Outcomes

- Death during hospitalization
- Deaths during hospitalization plus within 72 hours of LAMA
- Pneumothorax
- Aspiration pneumonia
- Length of hospital stay
- Incidence of nasal trauma, gastric distention, shock and air leaks
- Duration of bCPAP

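### The protocol reverses its Stage III primary and secondary outcomes between sections: death is primary in Sections 2 and 3, treatment failure elsewhere, and only treatment failure was powered

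*Protocol*

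**What the plan says.** **Death primary, treatment failure secondary**
- Section 2, Rationale, final paragraph: "Primary outcome will be death and secondary outcome will be treatment failure among children hospitalized with severe pneumonia in Ethiopia".
- Section 3, research question 2: "in reducing death (primary outcome) and treatment failure (secondary outcome) among hospitalized children in district hospitals in Ethiopia".

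**Treatment failure primary, death secondary**
- Summary, Statistical Analysis: "The primary outcome of the study is treatment failure and the secondary outcomes are death, pneumothorax, abdominal distention, nasal trauma, aspiration pneumonia". The Methodology row of the Summary agrees.
- Section 4.1, general objective: Stage III effectiveness is framed as a reduction in treatment failure.
- Section 4.2, Secondary Objectives: "To determine the effectiveness of bubble CPAP in reducing deaths in children admitted to frontline district hospitals".
- Section 5.2, Stage III, Primary outcome: "The primary outcome of the study is treatment failure".
- Section 5.2, Stage III, Secondary Outcomes: "Death during hospitalization" heads the list.
- Section 5.2, Stage III, sample size: treatment failure is named as the primary outcome, and 620 per arm is derived for 10% v 5%.

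**Mixed**
- Section 4.2, Primary Objectives: the first item is treatment failure in all children. The second is treatment failure together with mortality in children aged 1-12 months.

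**The concern.** Two sections reverse the two outcomes outright, and they do so in the same words. This is current text, not a change log, and no sentence says which statement governs.

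Three things are at stake. First, the trial's conclusion rests on whichever outcome is primary. The two can give different answers, because treatment failure also includes hypoxaemia with distress, an indication for ventilation, and leaving against advice while on the study treatment. Second, staff can see which treatment a child receives, and Section 6 plans three-monthly reports to the DSMB and an interim analysis six months into Stage III. A contradiction left in the text could therefore be settled with data in view. Third, an ethics board or DSMB member who relies on Sections 2 and 3 would take this for a mortality trial with 80% power, and the sample size section does not support that.

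**Working it through.** **Step 1. Which outcome does 620 per arm belong to?**

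Inputs, all from the Stage III sample size text: P1 = 10%, P2 = 5%, two-sided 5% (z = 1.96), 80% power (z = 0.84), ICC 0.003, cluster size m = 103.3.

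- Unpooled formula: (1.96 + 0.84)² × (0.10×0.90 + 0.05×0.95) / 0.05² = 7.84 × 0.1375 / 0.0025 = 431.2 per arm. The pooled-variance version gives 435, and with continuity correction 474.
- Design effect: 1 + 0.003 × (103.3 − 1) = 1.307.
- 474 × 1.307 = 619.5, which rounds up to 620.

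So 620 reproduces for treatment failure at 10% v 5%, with the continuity correction and the design effect that follows from the stated ICC. The printed design effect is 1.52, which gives 655 to 720 depending on the formula and does not reproduce 620. That mismatch is a separate matter; both values are carried below.

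The section contains no death rate, no effect on death and no power for death.

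**Step 2. What bound does the protocol put on the death rate?**

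One criterion of treatment failure is "If the patient died during hospitalization or within 72 hours of left against medical advice (LAMA"). Every death in that window counts as a failure, so under the assumed 10% failure rate the control death rate is at most 10%. The documents allow nothing narrower.

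**Step 3. Power for death with 620 per arm**

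Assumptions, not protocol figures: a control death rate p1 from 3% to 10%, halved by bubble CPAP (the same 50% reduction as for treatment failure). Effective size n = 620 / design effect, which is 474.4 at 1.307 and 407.9 at 1.52. With p̄ the mean of p1 and p2,

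power = Φ{ [ (p1 − p2)√n − 1.96 √(2p̄(1 − p̄)) ] / √(p1(1 − p1) + p2(1 − p2)) }

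Example, 5% v 2.5% at 1.307: (0.025 × 21.78 − 1.96 × 0.2687) / 0.2681 = 0.067, so power is 53%.

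| Control death v bubble CPAP | Power, DE 1.307 | Power, DE 1.52 |
|---|---|---|
| 3% v 1.5% | 34% | 30% |
| 5% v 2.5% | 53% | 47% |
| 6% v 3% | 61% | 54% |
| 8% v 4% | 74% | 67% |
| 9% v 4.5% | 79% | 73% |
| 10% v 5% (the treatment failure case) | 83% | 77% |

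The last row is the like-for-like comparator. It is 83% rather than 80% at 1.307 because this formula omits the continuity correction. With the correction, the 1.307 column reads 27% at 3%, 46% at 5%, 69% at 8%, 75% at 9% and 80% at 10%.

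**Step 4. Size needed if death were primary**

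The version that yields 620 (continuity correction, design effect 1.307) gives 2175 per arm at a control death rate of 3%, 1287 at 5%, 1064 at 6% and 787 at 8%.

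**The case against.** The strongest reply is that the operative parts of the protocol agree with each other. The Summary, the general objective, the first primary objective, the section headed Primary outcome and the sample size all name treatment failure. Death as primary appears only in a narrative paragraph and a parenthesis, and looks like text that was never reconciled. A statistician following the methods would test treatment failure. This stands: the point is an internal inconsistency that is easy to resolve, and the design does not leave the endpoint open. It does not remove the need to correct it, because the reversed statement appears twice and no rule of precedence is given.

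Three stronger readings are tempting, and the documents do not support them.

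- *Both outcomes would be tested as primary at 5%, which inflates the family-wise error.* No section proposes co-primary testing. Each version names one primary and one secondary outcome, and death is nested in treatment failure.
- *Power for death is known to be poor, at some particular figure.* The protocol gives no death rate. If nearly all failures were deaths, the loss would be small (79% v 83% at a 9% death rate). Only the direction is established, and only for the same relative reduction; a larger effect on death would change the figures.
- *Power for death on a t reference with 10 degrees of freedom can be set against the stated 80%.* By that method treatment failure itself has about 75% (design effect 1.307) or 69% (1.52). Part of such a gap therefore has nothing to do with which outcome is primary.

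**Conclusion.** The contradiction is real and is wrong as written. Sections 2 and 3 name death as the Stage III primary outcome. The Summary, the general objective, the Stage III outcome sections and the sample size name treatment failure. Section 4.2 places a mortality objective for ages 1-12 months under the primary heading. The weight of the text favours treatment failure, and the sample size fits only that reading.

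The 80% power does not apply to death. How much lower the power for death would be depends on an assumed control death rate and on the assumption of the same 50% reduction. That it is lower than for treatment failure at any control death rate below 10% follows from the protocol's own figures under that reduction.

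**What to change.** Make one protocol amendment with these edits:

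1. In the last paragraph of Section 2 and in research question 2 of Section 3, make treatment failure primary and death secondary, as in the Stage III outcome and sample size sections.
2. In Section 4.2, move the objective on treatment failure and mortality in children aged 1-12 months from Primary to Secondary Objectives and label it a subgroup objective. Without this, a mortality objective remains under the primary heading.
3. Add one sentence stating that the confirmatory claim of Stage III rests on treatment failure alone.

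The cost is a few sentences, with no change to sample size, conduct or data collection. The amendment should be made before outcome data are compared by arm.

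If the sponsor does intend death as the primary outcome, the outcome and sample size sections must change instead. The 80% power must then be withdrawn and restated for death, with a justified control death rate and effect.

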### 3. Research questions

1. How feasible, acceptable, and safe is bubble CPAP in treating children having severe pneumonia as perceived not only by patients' care-givers but also by physicians and nurses in the initial two stages?
2. How effective, feasible, acceptable, and safe is bubble CPAP for the treatment of young children under five with severe pneumonia compared to the WHO standard low-flow oxygen therapy in reducing death (primary outcome) and treatment failure (secondary outcome) among hospitalized children in district hospitals in Ethiopia?

3. How much resource and time is needed to institutionalize and maintain bubble CPAP as a routine practice in the health system?
4. What are the main potential challenges in using bubble CPAP at different levels of health care delivery system?

